### Clinical tests

The following routine clinical assessments are undertaken at each visit:

• Binocular single vision (BSV) testing − either stereovision or motor fusion (reflex convergence of the eyes in response to a base out prism);

• Best corrected visual acuity (VA) on an age-appropriate test;

• Measurement of the ocular misalignment using the Alternate Prism Cover Test (APCT);

• Measurement of how well the squint is controlled using the revised Newcastle Control Score (NCS)
[36] and the Mayo score
[37]. The NCS combines an estimate of observed frequency of the X(T) by parents (home control) with an assessment of the child’s ability to realign the eye following a cover test to induce misalignment (clinic control for distance and near fixation) − possible total NCS scores range from 0–9 (0–3 for home, 0–3 for clinic distance and 0–3 for clinic near control). On the Mayo score, the distance score (0 to 5) is combined with near score (0 to 5) to yield an overall control score ranging from 0 to 10. On both instruments, higher scores are indicative of poorer control.

### Inclusion criteria

• Age between ≥ 6 months and ≤ 16 years

• Evidence of X(T) on the basis of parental history and clinical examination

• No ongoing or planned amblyopia treatment

• VA of 0.500 or better on an age-appropriate logMAR-based test or, where uniocular testing is not possible, central steady maintained fixation when one eye is occluded

• NCS of ≥ 3

• Minimum of 15 dioptres misalignment in the distance

• Presence of near stereopsis documented using the preschool Randot Test if ≥ 3 years of age

• If < 3 years old must be able to overcome a base out prism (10, 15 or 20^)

### Exclusion criteria

• Age over 16 years

• Previous treatment for X(T)

• Constant XT (other than microtropia)

• VA of > 0.500 logMAR in either eye

• X(T) where near misalignment is >10 prism dioptres more than the distance misalignment

• Structural ocular pathology

• Significant neurodevelopmental delay

• Families planning to move out of area

### Recruitment and consent

Children referred from community screening, general practice or other health professionals are clinically assessed in the normal way when they attend their initial outpatient visit. Where appropriate, glasses are prescribed to correct any refractive error. Discussion about the management of the X(T) itself includes providing information about the study and the possibility of taking part. Parents who express an interest are then given written information and subsequently telephoned by a member of the study team to discuss any queries they may have once they have had time to read the documentation and talk things through with their families. All parents are given an appointment on a study recruitment clinic. At the recruitment clinic, eligibility is confirmed by checking the results of the initial routine clinical assessment against the inclusion criteria. Eligible parents are then asked if they would like to enter the study. Informed consent is obtained from those who decide to participate. Participants are also being identified from existing lists of patients who are already under follow-up and fulfil the eligibility criteria; we are adhering to the same information-giving and consent procedures as for new referrals.

The following routine clinical assessments are made in order to confirm the patient’s eligibility for the trial:

• BSV testing;

• Best corrected VA on an age-appropriate test;

• Measurement of the ocular misalignment using the APCT;

• Measurement of how well the squint is controlled using the NCS and Mayo scores.

Eligible families who do not wish to take part in the trial are asked whether they would consent to come back for a follow-up appointment after 9 months and allow us to use routine clinical data from that visit and their initial visit. Data from those who agree to this will be used to verify whether the recruited group is representative and to determine how many of those eligible but not recruited went on to have surgery during that 9-month period.

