**Methods:**

Design: an external pilot patient randomised controlled trial.

Setting: four UK secondary ophthalmology care facilities at Newcastle NHS Hospitals Foundation Trust, Sunderland Eye Infirmary, Moorfields Eye Hospital and York NHS Trust.

Participants: children aged between 6 months and 16 years referred with suspected and subsequently diagnosed X(T). Recruitment target is a total of 144 children over a 9-month period, with 120 retained by 9-month outcome visit.

Randomisation: permuted blocks stratified by collaborating centre, age and severity of X(T).

Interventions: initial clinical assessment; randomisation (eye muscle surgery or active monitoring); 3-, 6- and 9-month (primary outcome) clinical assessments; participant/proxy completed questionnaire covering time and travel costs, health services use and quality of life (Intermittent Exotropia Questionnaire); qualitative interviews with parents to establish reasons for agreeing or declining participation in the pilot trial.

Outcomes: recruitment and retention rates; nature and extent of participation bias; nature and extent of biases arising from crossover or loss to follow-up; reasons for agreeing/declining participation; variability of cure rates (to inform power calculations for a definitive RCT); completion rates of outcome measures.

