Surgical intervention and active monitoring together incur substantial costs to the UK National Health Service (NHS). For example, over 6,000 procedures were performed by the NHS on children under 16 years in 2007/8, of which around 1,000 are estimated to have been performed for X(T). The tariff rate for strabismus surgery is £800, and together with approximately 100,000 clinic visits annually for review of patients with X(T) (at a tariff cost of £120 per new patient and £60 per review: estimated average new:review ratio 1:8), the total cost to the NHS alone is almost £7.5 million annually. With the inclusion of societal and family costs, the management of X(T) is more costly. Our previous cohort study
[18,19] has demonstrated not only considerable variability in management between centres, but also a ‘therapeutic inertia’, with many children receiving no active treatment and many eventually defaulting from follow-up, contributing to high DNA (did not attend) rates. Without further research, inefficiencies in the use of NHS and societal resources used to manage X(T) are likely to remain.

The lack of trial-based evidence means that the true effectiveness of treatment in ameliorating or curing the condition is unknown. Moreover, even when surgery is the preferred course of action there is little agreement on whether immediate surgery is more effective than delaying the operation for a specified length of time or until a certain age. A pressing need for carefully planned clinical trials of treatment to improve the evidence base for the management of this condition has previously been identified
[27].

The current investigators hope to conduct such a trial, if feasible. Since the recruitment phase in any trial is one of the most challenging
[28,29], and given the potential recruitment barriers particularly inherent in paediatric
[30-33] or surgical
[34] trials, we are first undertaking the SamExo (**S**urgery versus **A**ctive **M**onitoring in Intermittent **Exo**tropia) pilot trial in order to assess feasibility and inform the design and conduct of a full-scale trial (
http://research.ncl.ac.uk/samexo/).

Parents of children with X(T) participating in a previous observational cohort study [The Improving Outcomes in Intermittent Exotropia (IOXT) study]

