### Participants and sample size

Children aged between 6 months and 16 years referred to the clinics with suspected X(T) from community screening, general practice or other health-care professionals, and subsequently diagnosed with X(T), as well as existing patients fulfilling the eligibility criteria. The parent/guardian provides written informed consent for participation in the study prior to any trial-specific procedures.

A formal power calculation was not performed for this feasibility study. It is not powered to detect a clinically or economically meaningful difference in the primary outcome between the surgical and active monitoring groups. Rather, the aim is to provide robust estimates of the likely rates of recruitment and retention, and to yield estimates of the variability of the primary and secondary outcomes to inform power calculations for a subsequent full-scale RCT. We originally estimated that over a recruitment period of 6 months (subsequently extended to 9 months) across four centres, we would be able to approach 240 patients who met the entry criteria. From their responses we would be able to determine whether the study is acceptable to parents and consequently whether it is possible to recruit patients and follow them up. We would also be able to estimate attrition rates. By approaching 240 children/parents we would be able to estimate the recruitment rate with a standard error no larger than 3.3%. Assuming that half of these children are actually recruited, we will be able to estimate the 6-monthly attrition rate with a standard error no larger than 4.3%.

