## Discussion

The optimum management of X(T) in children is contentious, with some clinicians recommending early surgery, some preferring to delay and others choosing to actively monitor. The lack of robust evidence to guide management and the poorly understood natural history of this condition renders it difficult for clinicians to offer clear advice to parents. Consequently, many children are observed without any treatment for extended periods because of the uncertainty surrounding the best course of action. The need for evidence from randomised studies has been acknowledged for some time now
[27], and this is the first attempt, as far as we are aware, to explore the potential for a RCT of surgery versus active monitoring in childhood X(T). We felt it would be inappropriate to undertake a full-scale study involving large numbers of participants and centres before first conducting a feasibility study. The SamExo pilot study will provide important pointers regarding how acceptable a RCT of immediate surgery versus deferred surgery/active monitoring will be to participants and clinicians.

The recruitment phase will give us a good indication of the proportion of eligible children/parents who would sign up to a full trial, the likelihood of them withdrawing from it and also an idea of how many we would need to approach over a given duration to achieve a specified sample size.

Equally pivotal will be the reasons why parents agree or decline the pilot trial, their perceptions of the need for and purpose of randomisation, their views on the nature of the information they received, and suggestions for improving future trials and refining the research question. Findings from these qualitative interviews will not only inform the design of a possible full trial but may also help investigators planning studies of surgical interventions, trials of other children’s eye conditions or paediatric trials in general.

Potential ethical issues include the fact that some of the children in the SamExo pilot study will be asked to wait up to 9 months before being offered surgery. We feel that this can be justified as our previous work has shown that less than 8% of children with X(T) had surgery within the first year following initial assessment when treated in a routine setting
[18]; in some centres, no children had surgery within 2 years of diagnosis

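### Decliners' existing initial-visit data are used only if the family also agrees to return at 9 months, which needlessly shrinks and self-selects the participation-bias comparison

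*Protocol article*

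**What the plan says.** Under Recruitment and consent, eligible families who do not want to join the trial are asked whether they would "come back for a follow-up appointment after 9 months and allow us to use routine clinical data from that visit and their initial visit". The next sentence states the use: "Data from those who agree to this will be used to verify whether the recruited group is representative". The same data are to show how many eligible but unrecruited children had surgery in those 9 months.

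Under Statistical methods, t-tests and Wilcoxon tests will compare the age and X(T) severity of families who consent with those of eligible families who refuse. Under Proposed outcome measures, the nature and extent of participation bias is one of the key outcomes of the pilot.

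**The concern.** The representativeness comparison needs age and severity only. Both are known once the initial clinical assessment is done, before a family decides about the trial. Nothing collected at 9 months is needed for it. As described, however, a family that would let its existing data be used but does not want to commit to another appointment contributes nothing. Statistical methods refers to eligible refusers as a group, while Recruitment and consent supplies only those who accept the combined request.

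The count of later surgery is limited to the same subset, although whether a child had an operation could be looked up in the hospital record without a visit.

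The article itself gives reason to think that a return visit is a real hurdle in this population. Its Background describes earlier experience of "many eventually defaulting from follow-up, contributing to high DNA (did not attend) rates". At stake is how far the pilot can say whether the families it recruits resemble those it does not. The investigators want that answer before designing the full trial.

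**Working it through.** **The plan's own figure.** The article gives no precision for the representativeness comparison. The nearest stated figure is for the recruitment rate: "we would be able to approach 240 patients who met the entry criteria", and with that number "we would be able to estimate the recruitment rate with a standard error no larger than 3.3" per cent. The binomial standard error is sqrt(p(1−p)/n). At p = 0.5 and n = 240 it is sqrt(0.25/240) = 3.23%, so the stated bound reproduces. Agreement to a return visit does not enter it.

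**Inputs.**
- Approached and eligible: 240 (Participants and sample size).
- Recruited: 144, from the abstract: "Recruitment target is a total of 144 children over a 9-month period, with 120 retained by 9-month outcome visit". Putting this beside the 240 is my assumption, because the 240 was first set for a 6-month recruitment period. It gives 144/240 = 60% recruited and 240 − 144 = 96 decliners.
- Alternative: Participants and sample size also assumes that half are recruited, which gives 120 recruited and 120 decliners.
- Share *a* of decliners who accept the combined request: not given; I take 25% to 100%.
- Difference δ between decliners who agree and those who do not: not given; I take 0.5 SD for illustration.
- Two-sided 5% level, as in Statistical methods; 80% power is my choice.

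**Loss of sensitivity.** With R recruited and m usable decliners, where m = a × (240 − R), the detectable standardised difference is (1.960 + 0.842) × sqrt(1/R + 1/m).

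| Share agreeing | R = 144: m | Detectable (SD) | R = 120: m | Detectable (SD) |
|---|---|---|---|---|
| 100% | 96 | 0.37 | 120 | 0.36 |
| 75% | 72 | 0.40 | 90 | 0.39 |
| 50% | 48 | 0.47 | 60 | 0.44 |
| 25% | 24 | 0.62 | 30 | 0.57 |

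For example, with R = 144 and m = 48: 2.802 × sqrt(1/144 + 1/48) = 2.802 × 0.1667 = 0.47.

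**Shift from self-selection.** The mean among agreeing decliners differs from the mean of all decliners by (1 − a) × δ. With δ = 0.5 SD:
- a = 75%: 0.25 × 0.5 = 0.125 SD
- a = 50%: 0.50 × 0.5 = 0.25 SD
- a = 25%: 0.75 × 0.5 = 0.375 SD

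At 50% agreement the shift of 0.25 SD is 0.25/0.1667 = 1.5 standard errors of the comparison. Depending on its sign, it could hide a real difference or suggest one that does not exist.

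**The case against.** The article condenses a fuller protocol, and the consent form is not shown, so the form may offer separate options. Statistical methods does not itself restrict the refusers to those who return. Declining parents may also be interviewed, and that is not tied to the 9-month visit. The follow-up data are described as routine, and many of these children stay under clinic review anyway, so the extra burden may be modest. Any fix that needs consent still leaves a volunteer sample.

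Much of this softens the point, but none of it removes it. Recruitment and consent describes one request and uses the data of those who agree to it. The interviews explore reasons for a decision, and interviewees are volunteers too. Residual selection is no reason to add an avoidable hurdle.

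Two stronger readings are tempting, and the documents do not support either.
- **The recruitment rate is inflated as well.** A reader might infer this because eligibility is confirmed and the trial offered at the recruitment clinic, so that families who never attend might drop out of the denominator. But a family that refuses both the trial and the return visit can still be counted as an eligible non-recruit. Participants and sample size bases the rate on eligible patients approached, and the Discussion speaks of "a good indication of the proportion of eligible children/parents who would sign up to a full trial". Recruitment and consent says that all parents receive an appointment and that eligibility is checked against results already obtained at the initial visit. Trial status shows that screened, eligible and agreeing patients are tracked. Restriction to clinic attenders would be inference.
- **The check is biased towards finding the recruited group representative.** This is plausible if decliners who will return resemble participants, but nothing in the article shows it. The remark on missed appointments concerns an earlier cohort in routine care, not families who declined a trial.

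**Conclusion.** The point holds for the participation-bias check and for the count of later surgery. As written, the plan gives up initial-visit data on every decliner unwilling to come back, although the planned comparison does not need a return visit. At an assumed 50% agreement, the detectable difference rises from about 0.37 to 0.47 SD with 144 recruited, and from 0.36 to 0.44 SD with 120. The decliner mean shifts by 0.25 SD if agreers and non-agreers differ by 0.5 SD. The agreement rate and that 0.5 SD are assumptions, and the direction of the shift is unknown. This is a modest weakness in a key pilot outcome, and it is cheap to correct. It does not touch the recruitment rate.

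**What to change.** Split the request to decliners into three separate permissions:
1. use of the existing initial-visit data;
2. a later look-up in the hospital record for surgery within 9 months;
3. a 9-month return visit.

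Base the age and severity comparison on everyone who grants the first and the surgery count on everyone who grants the second. Report how many refuse each, so that the remaining selection is visible. It would also help to state that the >60% recruitment criterion under Proposed outcome measures is read against the eligible patients approached, as in Participants and sample size.

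The cost is a reworded form and a minor ethics amendment. Recruitment was already under way, so decliners approached before the change fall under the old wording and should be identified as such in the report. Both the first and second permissions still depend on consent, so self-selection is reduced and not removed.

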### Interventions

#### Clinic appointments

Figure 
2 illustrates the schedule of study visits and corresponding assessments for the active monitoring and surgery arms. The assessments involve routine clinical measurements together with the evaluation of QOL using the Intermittent Exotropia Questionnaire (IXTQ)
[38], a health services use questionnaire (HSUQ) and a time and travel questionnaire (TTQ). Children in the active monitoring group will be offered surgery if a constant strabismus appears to be developing or parents request surgery and the responsible clinical team agrees that this is appropriate.

**Figure 2 F2:**
[figure not shown]
**Summary of study visits, assessments and interventions.** Abbreviations: HSUQ = health services use questionnaire; QOL = quality of life; RO = Research orthoptist; TO = treatment orthoptist; TTQ = time and travel questionnaire.

#### Eye muscle surgery

Surgery is performed by the local principal investigator (PI), or delegated deputy, according to agreed surgical formulae tailored to the clinical characteristics of the strabismus and the usual practice of the surgeon. Principles involved in the surgical treatment of children in the study have been agreed as follows:

• General anaesthesia

• Bilateral lateral rectus recession surgery to be performed for true distance exotropia

• Unilateral recess/resect surgery to be performed for other types of exotropia

• Standard sterile preparation of the operative site

• Conjunctival incisions

• Standard isolation and cleaning of muscle to be operated

• Muscle secured with 6/0 vicryl suture

• Amount of recession/resection assessed on the basis of the maximum distance angle according to table, modified according to standard practice of surgeon

• Measurement of amount of muscle adjustment to be checked post placement of scleral sutures

• Conjunctival incisions closed with vicryl sutures

• Topical anaesthetic and antibiotic drops given at the end of procedure

A surgical table (Table 
1) is being used with modification as appropriate to determine the amount of eye muscle movement to be performed depending upon the size of the angle of exotropia. Surgical technique is carefully recorded and monitored during the pilot with a view to standardising surgical technique, as far as it is possible to do so, in a full trial and provide a clear description of the intervention in subsequent reports.

**Table 1 T1:** Surgical table for use in the SamExo pilot trial

**Angle of deviation (dioptres)**	**Lateral rectus recession (mm)**	**Medial rectus resection (mm)**	**Bilateral lateral rectus recession (mm)**
20	4	3	4.5
25	5	4	5
30	5.5	4	6
35	6.5	4.5	6.5
40	7	4.5	7
50	8	4.5	8

#### Primary outcome visit

The final assessment (9-month outcome) will be conducted by a research orthoptist (RO) who is masked to the allocation of the child and has not otherwise been in contact with children enrolled in the study. The parent and child will be requested not to reveal the group allocation of the child to the RO prior to the assessment. While children have noticeably red eyes immediately following eye muscle surgery, it is recognised that this redness resolves within 6 weeks when this is a first procedure. Residual scarring of the conjunctiva following eye muscle surgery will be inconspicuous by 6 months.

#### Parent interviews

We are gathering qualitative data (primarily through telephone interviews) from parents to explore their reasons for either accepting or declining participation in the pilot study, their thoughts on randomisation and the study information received, and any ideas they may have for improving the trial. These data will inform the design of a full RCT. Whilst the principles of informed consent mean that individuals are not obliged to give a reason for their decision if they do not want to, we are inviting parents to take part in a telephone interview if they agree to this level of involvement. Without this information, it is difficult to see how the research design can be improved to make it more acceptable. These interviews are being conducted by a university researcher who is entirely separate from the clinical team, emphasising that parents’ decisions not to participate have been respected and reassuring that no attempt is being made to change their minds.

